**Part 1: Background**

Fluticasone-salmeterol has long been approved for the treatment of chronic obstructive pulmonary disease (COPD). In the US, GlaxoSmithKline markets two different inhalers containing fluticasone-salmeterol: Advair Diskus (first approved in 2000) and Advair HFA (first approved in 2006). The former, a dry powder inhaler, is approved for the indications of both COPD and asthma, while the latter, a metered-dose inhaler, is only approved for the indication of asthma. However, a small randomized controlled trial showed that Advair HFA had similar efficacy to Advair Diskus when treating COPD.^1^ Yet, metered dose inhalers have also been associated with more errors than dry powder inhalers.

Given ongoing clinical uncertainty, we will analyze the comparative effectiveness and safety of fluticasone-salmeterol delivered via metered-dose inhaler (Advair HFA) vs dry powder inhaler (Advair Diskus) among patients with COPD treated in routine clinical practice. The primary effectiveness outcome will be first moderate or severe COPD exacerbation; the primary safety outcome will be first pneumonia hospitalization. Secondary outcomes will include the annual rate of total moderate or severe COPD exacerbations (analyzed separately and together), first moderate exacerbation, first severe exacerbation, and annual rate of total pneumonia hospitalizations.

**Part 2: Protocol**

Protocol Version Date: 3/4/2024

Author(s): [name], [name], [name], [name], [name]

1. **Title:** The comparative effectiveness and safety of fluticasone-salmeterol via metered-dose vs. dry powder inhalers in COPD
2. **Core Research Team:** [name], [name], [name], [name], [name] (Implementation in the Aetion Evidence Platform: [name]; PI: [name])
3. **Aim(s)**

**Aim 1 (effectiveness):** To compare new users of fluticasone-salmeterol via metered-dose vs. dry powder inhalers on the outcome of first moderate or severe COPD exacerbation.

**Aim 2 (safety)**: To compare new users of fluticasone-salmeterol via metered-dose vs. dry powder inhalers on the outcome of first pneumonia hospitalization.

1. **Data source**: Optum Clinformatics claims database January 1, 2007-November 30, 2023. The study will begin in 2007 since that is the first full year after Advair HFA was approved (Advair Diskus was approved in 2000). Thus, both products were on the US market throughout the study period.
2. **Study Design Diagram:** see Appendix Figure 1
3. **Cohort Identification**

**6.1 Cohort Summary**

All patients with COPD, defined by 3 outpatient claims or 1 inpatient claim in the prior 3 years (PPV 0.82 [0.72-0.89]),^2^ who initiated a prescription for fluticasone-salmeterol (Advair HFA) (exposure) vs. fluticasone-salmeterol (Advair Diskus) (referent) between January 1, 2007 and November 30, 2023. We will require a 180-day washout period for both the exposure and the referent. We will also require 180 days of continuous insurance coverage prior to cohort entry. We will include patients who received other therapy in the baseline period (whether single-agent inhalers [ICS, LAMA, LABA], LAMA-LABAs, or triple therapy). In other words, we will include patients who may be stepping up therapy (from monotherapy), stepping down therapy (triple therapy), or switching (from LAMA-LABA). Following other studies, we will exclude patients who are less than age 40 to increase the specificity of COPD diagnoses. This will help further ensure that patients entering the cohort are receiving triple therapy for COPD rather than another respiratory condition.

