***Study period:***

Baseline Period: The baseline period is defined as 180 days prior and up to and including the cohort entry date [-180, 0] unless otherwise noted in the design diagram.

Follow up Period: The follow-up period starts 1 day after the cohort entry date and continues until censoring. For further details on censoring, see section 8.2.

***Note:*** All diagnosis, procedure and generic names of drugs are given in the file named “Protocol Appendix.”

| Steps |  |
| --- | --- |
| **6.2.1** | **Patients with prescription for Advair HFA/Diskus**  *Advair HFA is the exposure and Advair Diskus is the reference* **(fills of both on cohort entry are not allowed)**  **Date of prescription is called the index date**  [assessed between January 1, 2007 and November 30,2023]  *Appendix Table 1 “Exposure definitions,” variables names: Advair HFA, Advair Diskus* |
| **6.2.2** | **Exclude patients who do not have continuous insurance enrollment during baseline period**  [assessed between 180 days prior up to and including index date (-180, 0)] |
| **6.2.3** | **Exclude patients with no prior diagnosis of COPD**  [assessed 3 years prior to and including the index date (-1095, 0)]  *Appendix Table 2 “Exclusion criteria,” variable name: Diagnosis of COPD* |
| **6.2.4** | **Exclude patients who are under the age of 40**  [assessed on the index date (0, 0)] |
| **6.2.5** | **Exclude patients who received another ICS-LABA script (besides Advair HFA or Advair Diskus)**  [assessed between 180 days prior up to and including index date (-180, 0)  *Appendix Table 2 “Exclusion criteria,” variable name: ICS-LABA besides Advair* |
| **6.2.6** | **Exclude patients who started a LAMA, LAMA-LABA, or ICS-LAMA-LABA on the cohort entry date**  [assessed on the cohort entry date (0,0)] |

1. **Covariates**

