The baseline covariate assessment period for all measures will start 180 days before cohort entry and will stretch up to and include the day of cohort entry with the following exceptions: (1) We will assess age, sex, race, region, year of cohort entry, and index prescription by a pulmonologist only on the day of cohort entry; (2) We will assess the presence of any prior asthma diagnosis using all available data and stretching up to (and including) the day of cohort entry. Diagnosis based covariates will be defined using any care setting and any diagnosis position unless otherwise specified. All codes for these variables are provided in Appendix Table 3, “Covariates.” The variable names are as listed below in Table 1. All variables listed below will be included in our propensity score model. We will use a missing indicator in our propensity score model in the case that data are missing for any covariates.

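### COPD entry may rest on codes up to three years old, and the primary weights do not directly measure how recent, frequent or inpatient that coding was, so arms may differ in the share who truly have COPD

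*Protocol*

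**What the plan says.** Section 6.1 (Cohort Summary) defines COPD as "defined by 3 outpatient claims or 1 inpatient claim in the prior 3 years (PPV 0.82 [0.72-0.89"]). Step 6.2.3 uses the same window, "assessed 3 years prior to and including the index date (-1095, 0"). Neither place asks for a COPD code close to the index fill. On enrolment, section 6.1 says "We will also require 180 days of continuous insurance coverage prior to cohort entry", and step 6.2.2 repeats the 180 days.

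The Background (Part 1) says that Diskus is approved for COPD and asthma, and that "the latter, a metered-dose inhaler, is only approved for the indication of asthma".

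The Covariates section says "The baseline covariate assessment period for all measures will start 180 days before cohort entry". Among its few exceptions, prior asthma is searched in all available data. No exception extends the window for COPD coding. The same section says "All variables listed below will be included in our propensity score model", so Table 1 is the propensity model. Table 1 lists no time since last COPD code, COPD claim count, inpatient or outpatient qualification, or length of observable history.

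**The concern.** A patient can enter on three outpatient COPD codes that all precede the 180-day covariate window, and can start the inhaler for another reason. Such patients are less certain to have COPD than those with many recent codes or an admission. Because the labels differ, prescribers may have chosen HFA more often where the working diagnosis was asthma. If so, the arms differ in their share of true COPD, and the weights can correct this only through proxies.

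The enrolment rule adds to this. With 180 guaranteed days out of 1095 (180/1095 = 16%), a patient with a short history can qualify only on recent codes, while one with a long history can qualify on old ones. The sensitivity of the asthma covariate also depends on the history available.

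At stake is the primary effectiveness hazard ratio, in a comparison where the Background cites evidence of similar efficacy. A shift of a few per cent could affect its reading. Any such bias would arise from who is in the cohort, and none of the sensitivity analyses varies the COPD entry definition.

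**Working it through.** **The plan's own figure.** The PPV of 0.82 (0.72-0.89) is cited without counts, so it cannot be re-derived. It is coherent as a binomial proportion: a Wilson 95% interval gives these limits for counts from about 59/72 to 68/83.

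**What Table 1 covers.**
- Recent inpatient COPD coding: partly covered. Severe exacerbations in the 180-day baseline are, by the protocol's definition, admissions with COPD in the primary position.
- Asthma: covered, any prior diagnosis in all available data.
- COPD care: covered by proxies (LAMA, LAMA-LABA, triple therapy, roflumilast, spirometry, oxygen, pulmonary rehabilitation, pulmonologist visits and prescriber).
- Moderate exacerbations: listed, but section 8.1.A builds them from prednisone fills, so they do not show that COPD was coded.
- Outpatient COPD coding, recent or old: no direct measure. The same holds for claim count, qualifying route and observable days.

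**Possible size.** The protocol gives no arm-specific PPVs or event rates, so these inputs are assumed. Let q1 and q0 be the true-COPD shares in HFA and Diskus that remain after weighting, and r the event rate without COPD relative to that with COPD. With a true hazard ratio of 1 and constant rates:

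apparent HR = [q1 + (1 - q1)r] / [q0 + (1 - q0)r]

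For q1 = 0.72, q0 = 0.89, r = 0.5: (0.72 + 0.14)/(0.89 + 0.055) = 0.860/0.945 = 0.910.
For r = 0.8: 0.944/0.978 = 0.965.
For r = 1.2: 1.056/1.022 = 1.033.

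| q1 / q0 | r = 0.5 | r = 0.8 | r = 1.0 | r = 1.2 |
| --- | --- | --- | --- | --- |
| 0.72 / 0.89 | 0.910 | 0.965 | 1.000 | 1.033 |
| 0.77 / 0.83 | 0.967 | 0.988 | 1.000 | 1.012 |
| 0.82 / 0.82 | 1.000 | 1.000 | 1.000 | 1.000 |

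The first row borrows the ends of the PPV interval only to mark an extreme gap. That interval expresses sampling error, not a difference between arms.

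**How much would direct measures help?** A simulation (600,000 patients, true-COPD share 0.82, HFA log-odds 0.4 to 1.0 higher without COPD, r = 0.5) gave weighted hazard ratios of 0.971, 0.947 and 0.924 with proxies like those in Table 1. After recency and count were added they were 0.978, 0.959 and 0.943. The share of bias removed is 0.007/0.029 = 24%, 0.012/0.053 = 23% and 0.019/0.076 = 25%. The simulation assumes the arm differential and the proxy strengths, so it shows only that the covariates may help in part. It does not show that a bias exists.

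**The case against.** The strongest reply is that the label argument runs through asthma, and asthma is already in the weights from all available data, beside many markers of true COPD. This has force. A reader might infer that the weights cannot balance the likelihood of COPD, or that Table 1 holds nothing on recency or setting. The protocol does not support either reading, given the 180-day severe exacerbations and the proxies above. What remains is that proxies are indirect, and a patient without asthma codes may still hold only old COPD codes.

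A reader might also infer that the bias favours HFA. That needs r below 1. A patient with asthma and no COPD who fills a 5-14 day prednisone course counts as a moderate exacerbation, so r may be near or above 1. Direction is open, and the argument is stronger for severe exacerbations, which need a primary COPD code.

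Nor does the PPV show that 18% of this cohort lacks COPD. It comes from a validation study, and this cohort is further restricted to age 40 and over and to ICS-LABA initiators. The three-year window is no error either, since it is part of the definition to which the PPV is attached.

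Step 6.2.3 says "Exclude patients with no prior diagnosis of COPD", which might be read as a looser rule than section 6.1. It points to a definition in Appendix Table 2 that is not at hand, so no contradiction is shown.

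Finally, the plan has analyses with and without asthma and spirometry, and a high-dimensional propensity score analysis that might pick up COPD codes. They test the concern in part, but they leave the primary weights unchanged.

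**Conclusion.** The point holds as a possible residual imbalance that the primary weights do not address directly. The protocol establishes the long code window, the short enrolment requirement, the label difference and the absence of four direct variables from Table 1. It does not establish that the arms differ in true COPD after weighting, by how much, or which way the hazard ratio would move.

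The illustrative range of 0.91 to 1.03 rests on assumed shares and assumed r. With a more modest gap (0.77 against 0.83) it is 0.97 to 1.01, and with equal shares or r = 1 there is no bias. This is a worthwhile, inexpensive improvement to the primary analysis, not a flaw that invalidates the design.

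**What to change.** Add four variables to Table 1 and the CBPS model, and report their balance by arm before and after weighting:
- time since the last COPD claim, or an indicator of any COPD claim in [-180, 0];
- number of distinct COPD claim dates in [-1095, 0];
- inpatient or outpatient qualification;
- observable days before entry, capped at 1095.

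Add one sensitivity analysis restricted to patients with a COPD claim in [-180, 0]. It is needed as well, because the added covariates would probably remove only part of any bias.

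The COPD claims are already read for eligibility, so the cost is four derived variables, a refit of the weights with its balance assessment, and one extra run. The downside is a possible small loss of effective sample size, and fewer patients in the restricted run.

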**6.2 Important steps for cohort creation**

***Cohort entry date:*** The cohort entry date is of the first claim for fluticasone-salmeterol (Advair HFA) (exposure) vs. fluticasone-salmeterol (Advair Diskus) (referent) between January 1, 2007 and November 30, 2023

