| **4** | Exclude the first 30 and 60 days after cohort entry. | Patients may receive ICS-LABAs when their symptoms are bad (but before a true moderate or severe COPD exacerbation). We will assess whether any differences between Advair Diskus and Advair HFA exist when we exclude these early exacerbations. | This allows us to focus on the long-term effectiveness of these maintenance therapies. | Follow-up time will be low because patients discontinue their inhalers so frequently. We may not have sufficient power to detect small treatment effects in this analysis. |
| **5** | Alter the definition of a moderate exacerbation: (a) require an office or ED visit before the prednisone fill; (b) require both prednisone (5-14 days) and a respiratory antibiotic; (c) count either a prednisone script (5-14 days) or a respiratory antibiotic script | This will allow us to assess the robustness of the results to variations of the outcome definition. | Each of these outcome definitions has been employed elsewhere in the literature. | (a) We will exclude many patients who have moderate COPD exacerbations but do not come into clinic. (b) We will exclude many patients who are having moderate exacerbations (antibiotics + steroids are only recommended for patients meeting specific criteria such as purulent sputum); (c) We will include patients who receive antibiotics for reasons having nothing to do with COPD exacerbations |
| **6** | Alter the definition of a severe exacerbation: allow for a COPD diagnosis in any position for the hospitalization | This will allow us to assess the robustness of the results to variations of the outcome definition. | The outcome definition in the primary effectiveness analysis may exclude patients who are having a COPD exacerbation but are admitted for a different primary reason (e.g. MI). | This is a less specific definition than the one we employed since many patients will have a code for COPD during a hospitalization even though they are not having an exacerbation. |

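### New use rests on a 180-day look-back: earlier ICS-LABA use is neither adjusted for nor tested, and for products other than Advair it is not excluded

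*Protocol*

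**What the plan says.** Aim 1 is "To compare new users of fluticasone-salmeterol via metered-dose vs. dry powder inhalers on the outcome of first moderate or severe COPD exacerbation"; Aim 2 uses the same population for pneumonia hospitalization. Four parts of the protocol determine who counts as a new user.

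- **Section 6.1:** "We will require a 180-day washout period for both the exposure and the referent". The guaranteed history is of the same length: "We will also require 180 days of continuous insurance coverage prior to cohort entry".
- **Section 6.2, cohort entry date:** "The cohort entry date is of the first claim for fluticasone-salmeterol (Advair HFA"), or for Diskus, between January 1, 2007 and November 30, 2023.
- **Step 6.2.5:** "Exclude patients who received another ICS-LABA script (besides Advair HFA or Advair Diskus"), assessed in (-180, 0).
- **Covariates section and Table 1:** "The baseline covariate assessment period for all measures will start 180 days before cohort entry". The exceptions are some items read on day 0 and one long look-back: "We will assess the presence of any prior asthma diagnosis using all available data". The inhaler classes in Table 1 are LAMA, LABA, ICS, LAMA-LABA and ICS-LAMA-LABA. ICS-LABA is not listed.

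The sensitivity analyses vary the grace period, the follow-up rule, the outcome definitions and the balancing method. None varies the washout or the look-back.

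**The concern.** Within the 180 days an ICS-LABA covariate would be redundant, because those users are excluded. Before that window the protocol does nothing with ICS-LABA history. Someone treated with another ICS-LABA until seven months before entry is handled exactly like someone who never had one.

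Previous users are a selected group. They may have stopped because of poor control, intolerance or low persistence, or they may have tolerated the class well and simply lapsed. If their share differs between HFA and Diskus starters, part of the device contrast in both primary outcomes reflects treatment history. The two products contain the same drugs, so a true difference may be small and even a modest spurious HR could affect interpretation.

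Section 6.1 describes entrants as stepping up, stepping down or switching. It does not mention returning ICS-LABA users, so the protocol does not show that including them was intended.

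**Working it through.** The protocol gives no sample size, event count or share of previous users, so there is no figure to reproduce. The check has two parts.

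**1. What happens to each kind of earlier use**

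| Earlier ICS-LABA use | Treatment under the protocol |
| --- | --- |
| Any product, within 180 days | Excluded (washout in 6.1; step 6.2.5) |
| Other ICS-LABA, before day -180, visible in the data | Not excluded, not in Table 1 |
| Advair, before day -180, visible in the data | Barred if the entry rule in 6.2 literally means the earliest Advair fill in the study period; enters unadjusted if it means the earliest fill after the washout |
| Any product, before 2007 or before enrolment | Not visible; enters on any reading |

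The second row is open however section 6.2 is read. The third depends on how 6.1 and 6.2 fit together: a literal earliest-fill rule leaves the Advair washout little to do, while a washout rule makes the wording of 6.2 inexact. The last row cannot be closed with these data. The data start on January 1, 2007, so the earliest entry with 180 days of baseline is June 30, 2007, and Diskus use in 2000-2006 cannot be seen.

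**2. How large a bias could be**

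For one binary unmeasured confounder, a true HR of 1.00 appears as approximately

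B = [1 + p_HFA × (RR − 1)] / [1 + p_Diskus × (RR − 1)]

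Here p is the share with earlier ICS-LABA use, and RR is the event-rate ratio in such patients after the planned adjustment. **All values of p and RR are assumptions.**

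| p_HFA | p_Diskus | RR | Calculation | B |
| --- | --- | --- | --- | --- |
| 0.30 | 0.20 | 1.2 | 1.06 / 1.04 | 1.019 |
| 0.30 | 0.20 | 1.5 | 1.15 / 1.10 | 1.045 |
| 0.20 | 0.20 | any | equal terms | 1.000 |
| 0.20 | 0.30 | 1.2 | 1.04 / 1.06 | 0.981 |
| 0.20 | 0.30 | 1.5 | 1.10 / 1.15 | 0.957 |
| 0.30 | 0.10 | 2.0 | 1.30 / 1.10 | 1.182 |
| 0.10 | 0.30 | 2.0 | 1.10 / 1.30 | 0.846 |

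The last two rows are deliberately severe: a threefold difference in shares and a doubled rate that the other covariates leave untouched. With moderate inputs the shift is 2% to 5%. It vanishes if the shares are equal, and its sign flips if the shares are reversed or if previous users have a lower rate (RR below 1).

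**The case against.** The strongest reply is that the 180-day washout is openly stated, identical in both arms and set in an active-comparator design. The propensity model also holds good proxies for earlier poor control: baseline exacerbations, 180-day inhaler use, SABA fills, asthma on all data, pulmonologist prescribing and year of entry. The two entry-period subgroups and the high-dimensional propensity score add something. Read literally, the first-claim rule already removes every earlier Advair user visible in the data. Appendix Figure 1 and the appendix tables are not shown, and section 6.2 lets the diagram set other windows.

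Most of this stands as mitigation. None of it measures earlier ICS-LABA use, no longer look-back is stated for the high-dimensional score, and the covariates section names asthma as the only item read in all available data. The first-claim rule does not touch other ICS-LABAs.

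Two stronger readings are tempting and not supported.

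- A reader might infer that more previous users start HFA, because Diskus came in 2000 with a COPD indication and HFA in 2006 without one. The protocol has no data on which device previously treated patients start, and a lapsed Diskus user may simply restart Diskus.
- A reader might infer that restarts after more than 180 days are common, because the early-exclusion sensitivity analysis warns that "Follow-up time will be low because patients discontinue their inhalers so frequently". That sentence is about stopping. It says nothing of restarts or the length of gaps, so such restarts are plausible but their frequency is unknown.

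**Conclusion.** The gap is real. Both aims claim new users, yet visible ICS-LABA use before day -180 is not adjusted for or tested in a sensitivity analysis, and for products other than Advair it is not excluded. Whether visible earlier Advair use is excluded depends on which of sections 6.1 and 6.2 governs.

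The direction of any bias is open. Its size is probably modest: 2% to 5% in the HR either way on the moderate inputs, before allowing for anything the existing covariates absorb beyond the assumed RR. Those figures rest wholly on assumed shares and rate ratios, and equal shares would give no bias. This does not invalidate the design. It is a worthwhile improvement because claims already held can show whether the arms differ.

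**What to change.** 1. Keep the 180-day entry rule.
2. Reconcile sections 6.1 and 6.2: state whether an Advair claim visible before day -180 bars entry.
3. Add one term to Table 1 and the CBPS model: any ICS-LABA fill in all available data up to day -181, including Advair if the washout reading applies. Report it by device before and after weighting.
4. Add one sensitivity analysis of both primary outcomes, restricted to patients with no ICS-LABA claim before entry over a longer look-back, with enrolment required for all of it (for example 365 days or more). Without that requirement, patients with only 180 days of history would be counted as never users by construction.

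The cost is one claims-derived covariate, one more run of the same model and a repeat of the balance check. The covariate's look-back will vary between patients, as is already accepted for asthma. The restricted run will be smaller. Use before 2007 or before enrolment stays unseen, so the fix reduces the problem without removing it.

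### No Table 1 covariate records whether a LAMA-containing inhaler was still in hand at cohort entry, so the weights cannot be shown to balance current against lapsed use

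*Protocol*

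**What the plan says.** - **Who enters.** Section 6.1 keeps patients with other inhaled therapy in the baseline period and describes them as possibly "stepping up therapy (from monotherapy), stepping down therapy (triple therapy), or switching (from LAMA-LABA").
- **Who is removed on day 0.** Step 6.2.6 reads "Exclude patients who started a LAMA, LAMA-LABA, or ICS-LAMA-LABA on the cohort entry date". It concerns starters on that date. Patients who already used such a product, recently or long before, stay in.
- **Window.** In the Covariates section, "The baseline covariate assessment period for all measures will start 180 days before cohort entry", up to and including day 0. There are two exceptions. The first is "We will assess age, sex, race, region, year of cohort entry, and index prescription by a pulmonologist only on the day of cohort entry". The second is "We will assess the presence of any prior asthma diagnosis using all available data". Neither covers maintenance inhalers.
- **What enters the model.** "All variables listed below will be included in our propensity score model". The Statistical analysis section confirms that the Table 1 variables are the predictors in the CBPS model.
- **What Table 1 lists.** The maintenance inhalers appear as five bare class names. The relievers (SABA, SAMA, SAMA-SABA) are labelled as fills. A separate block covers the 30 days before entry, but it holds only exacerbations and respiratory antibiotic fills.
- **Coding.** "All codes for these variables are provided in Appendix Table 3, “Covariates", and that appendix is not shown.

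**The concern.** Concurrent long-acting therapy at entry plausibly marks disease severity and may itself alter the risk of exacerbation. A patient who starts Advair with a LAMA in hand may be going on to three classes of drug. A patient whose LAMA ran out months earlier starts two. Over a 180-day window the two can have the same covariate value.

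The protocol itself treats both elements as important. Step 6.2.6 makes starting a LAMA-containing product on day 0 a reason for exclusion, and the 30-day block in Table 1 shows that recency matters for exacerbations and antibiotics. Neither idea is carried over to the maintenance inhalers.

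If current use differs by device among prior users (for instance because prescribers match the new inhaler to one already in use), the weighted arms could agree on every Table 1 entry and still differ in the share with concurrent LAMA therapy. The balance comparison used to choose CBPS-IPTW cannot reveal imbalance in a variable that was never built. None of the listed subgroups is defined by concurrent LAMA either.

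**Working it through.** The protocol states no figure on this point, so there is nothing of its own to reproduce. The check has two parts.

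**1. Does either possible coding separate current from lapsed users?** Assume 30-day fills.

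| Patient | LAMA fills on days | Supply ends about | Any use | Fill count |
|---|---|---|---|---|
| A | -170 | day -140 | 1 | 1 |
| B | -10 | day +20 | 1 | 1 |
| C | -170, -140, -110 | day -80 | 1 | 3 |
| D | -70, -40, -10 | day +20 | 1 | 3 |

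A and B are identical under both codings, and so are C and D, yet A and C had lapsed and B and D had supply in hand. A fill count tends to be higher in continuing users, so it separates the groups in part, but it carries no date.

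**2. How large could the effect be?** All inputs are assumptions; the protocol gives none of them.

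- q: share of the cohort with any LAMA use in the window
- p1, p0: share of those users with supply in hand at entry, in each arm
- RR: net event-rate ratio, in hand versus lapsed

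Treating the hazard ratio as a ratio of mean rates, with any LAMA use perfectly balanced:

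bias factor = [1 + q·p1·(RR − 1)] / [1 + q·p0·(RR − 1)]

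Among prior LAMA users only (q = 1), RR = 1.3:
- p1 = 0.75, p0 = 0.60: 1.225 / 1.180 = 1.038
- p1 = 0.70, p0 = 0.50: 1.210 / 1.150 = 1.052

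Whole cohort with q = 0.5, RR = 1.3:
- p1 = 0.75, p0 = 0.60: 1.1125 / 1.0900 = 1.021
- p1 = 0.70, p0 = 0.50: 1.1050 / 1.0750 = 1.028

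Wider range, with q from 0.2 to 0.6, p0 = 0.60 and RR from 0.7 to 1.5 (RR below 1 allows the benefit of the LAMA to outweigh its role as a marker of severity):

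| Gap p1 − p0 | Lowest factor | Highest factor |
|---|---|---|
| 0 points | 1.000 | 1.000 |
| 10 points | 0.980 | 1.025 |
| 20 points | 0.960 | 1.051 |

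The extremes come from q = 0.6. For example, at 20 points they are (1 − 0.144)/(1 − 0.108) = 0.960 and 1.240/1.180 = 1.051. The direction depends on which device has more current users and on whether RR lies above or below 1.

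**The case against.** **The coding is not visible.** A reader might infer that maintenance therapy enters the model only as any use in 180 days. The labels point that way, since relievers are called fills and maintenance classes are not, but no text says so. The coding is in Appendix Table 3, and section 6.2 also lets the design diagram alter the baseline window. Neither is shown. This stands against that inference. It does not remove the gap: the Covariates section applies one window to all measures with two stated exceptions, and a fill count over that window would still lack recency.

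**Table 1 already separates the groups named in section 6.1.** It does so by class: LAMA, LAMA-LABA and ICS-LAMA-LABA are separate entries. This stands. What remains is current versus lapsed use within a class.

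**Supply in hand does not show intent.** A reader might infer that a patient with LAMA in hand on day 0 is adding Advair and so starts triple therapy, or that a single step-up, switch or step-down variable would do the same work. The documents support neither. A patient whose LAMA is replaced by Advair may also have supply reaching day 0, and only later refills could tell the two apart. Those fall after entry and cannot serve as baseline covariates.

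**Other covariates and analyses may absorb part of it.** Exacerbation history, 30-day exacerbations, home oxygen, pulmonologist visits and prescription drug claims are all in the model and plausibly carry some of the severity signal. The high-dimensional propensity score sensitivity analysis may pick up more. Both points are fair, but that analysis does not specify its inputs and does not alter the primary weights.

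**No imbalance is shown.** This is correct. Nothing in the protocol indicates that current LAMA use differs by device.

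**Conclusion.** The point holds as a gap in the listed covariate set. As written, Table 1 has no variable designed to separate patients with a LAMA-containing product in hand at entry from those whose supply had lapsed, and the planned balance check could not reveal a difference between devices in that respect.

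The likely size is modest. With half the cohort prior LAMA users, a 15-20 point gap in current use and a net 1.3-fold rate, the hazard ratio moves by about 2-3%. With equal current use in the two arms it does not move. These inputs are assumed, and the formula gives no credit to the other severity covariates, which may carry part of any difference. It would be wrong to read this as evidence that the device comparison is biased, because the protocol holds no data on current use by device. The case for acting is that two devices delivering the same drugs may differ little, that a larger cohort would not shrink such a bias, and that the needed fills already lie in the baseline window. It is a change that should be made; it does not invalidate the design.

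**What to change.** - Keep the five class variables as they are, and state in the protocol text whether each is any use or a fill count.
- Add to Table 1 and to the CBPS model an indicator, for each of LAMA, LAMA-LABA and ICS-LAMA-LABA, that dispensed days' supply reaches day 0, with the grace period stated. Recency of the last fill in the class can be added as an option.
- Report balance on these indicators by device, before and after weighting. That table alone would show whether current use differs by device.
- Describe the new variables as separating current from lapsed supply only, and make no claim that they identify add-on, replacement or step-down.

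Cost: a few derived variables, correlated with those already in the model, and one refit of the weights. Since CBPS-IPTW was chosen on balance, effective sample size and extreme weights, those metrics need to be rechecked after the refit.
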